#### Study inclusion criteria

Documented genetic diagnosis of CDD based on pathogenic variants in the *CDKL5* gene;age range 3–50 years; clinical diagnosis of CDD and demonstrated *CDKL5* pathogenic variant;drug-resistant seizures;stable drug regimen for 4 weeks prior to starting the study;written informed consent signed by the parent/legal guardian/representative prior to the screening visit;the caregiver must be able to understand the instructions and consciously participate in the study.

#### Study exclusion criteria

Enrolment in another clinical trialorganic GI disorders (i.e., food allergies, celiac disease)special dietsuse of percutaneous endoscopic gastrostomy tube (PEG)use of antibiotics or probiotics in the month prior to enrolment

### Study procedures

The schedule of activities planned during the study is summarized in Table 1.

**Table 1 tab1:** Summary of measures and instruments used in the present study.

Study period					
Enrolment		Intervention period			
Timepoint	T0	T1	T2	T3	T4
Enrolment:					
Eligibility screen	X				
Informed consent	X				
Demographics	X				
Medical history	X				
Concomitant medication	X				
Intervention:					
ALAC, FOS, and inulin supplementation		X			
ALAC, FOS, inulin and NaB supplementation				X	
Assessments					
Dietary survey	X	X	X	X	X
Gastrointestinal Severity Index (GISI) (16) scale	X		X		X
Bristol Stool Form Scale (BSFS) (16)	X	X	X	X	X
Clinical global impression– improvement scale (CGI-I) (16)	X		X		X
Motor-Behavioral Assessment Scale (MBAS) (16)	X		X		X
CDKL5 severity assessment (CDD-SA) (29)	X		X		X
Sleep Disturbance Scale for Children (SDSC) (16)	X		X		X
Daily Seizure diary	X	X	X	X	X
Parenting Stress Index questionnaire (PSI-SF) (16)	X				x
Feces collection	X	X	X	X	X
Dried blood spots collection	X	X		X	
Adverse effects	X	X	X	X	X

T0, screening/baseline; T1, first supplementation (MF1); T2, wash-out period; T3, second supplementation (MF2); T4: wash-out period.

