**Methods and analysis:**

The protocol involves a two-step treatment strategy: a 12-week supplementation with alpha-lactalbumin (ALAC), fructooligosaccharides (FOS), and inulin to reduce inflammation, followed by a 12-week supplementation with ALAC/FOS/Inulin plus Sodium butyrate (NaB), to restore the balance of the gut microbiota. Clinical parameters, including seizure frequency, sleep disturbances, and GI discomfort, will be evaluated. Stool samples will be collected to analyse the gut microbiome. Primary objectives are to determine whether supplementation with ALAC/FOS/inulin alone or in combination with NaB can improve neurological features in CDD and to explore their effects on gut microbiota composition. Our study aims to provide insights into the potential benefits of targeting the gut-brain axis in CDD and offer new therapeutic options to improve seizure control and associated comorbidities.

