### Trial design

This is a 32-week single-arm, open-label clinical trial of ALAC/FOS/Inulin (MF1, Kolfarma s.r.l. - Italy) vs. ALAC/FOS/Inulin/NaB (MF2, Kolfarma s.r.l. - Italy) aimed at restoring gut homeostasis and gut community health (Figure 1). The intervention will be conducted in a single investigational study centre in Italy, namely the Child and Adolescent Childhood Neurology and Psychiatry Unit at ASST Grande Ospedale Metropolitano Niguarda in Milan, Italy.

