**Figure 1 fig1:**
[figure not shown]
Trial design. We planned a 32-week longitudinal intervention based on two sequential interventions. A 12-weeks supplementation has been selected to ensure a sufficient duration for evaluating meaningful clinical changes (according to the primary and secondary outcomes). Wash out periods have been designed to verify the duration of clinical and gut microbiota changes after supplement discontinuation. DBS, dried-blood spot; ALAC, alpha-lactalbumin; FOS, Fructooligosaccharides; MF, Medical Food; NaB, Sodium butyrate.

We planned an interventional study as follows: a 12-week supplementation period with MF1, 4-week washout, 12-week supplementation with MF2, and a final 4-week washout. Patients will undergo full clinical assessments at baseline (enrollment, before starting the first supplementation), after the first supplementation and at the end-of-treatment visit, 1 week after the last supplementation. Stool and dried-blood spot (DBS) samples, food diary, and GI scales will be collected at scheduled time points, as described in the Study Procedures’ paragraph. Gut microbiome characterization, SCFAs (short-chain fatty acids) quantification, clinical scales and dietary intake will be assessed.

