### Efficacy endpoints

The primary outcomes of the study are:

To evaluate the number of CDD patients considered treatment responders (seizure reduction ≥50%, ≥75% or ≥100% from baseline in monthly seizure counts) during the 12-week treatment period in 1st and 2nd round of supplementation. With regard to seizure counting, in order to improve its reliability, seizures characterized by a motor component of sufficient intensity and/or duration to potentially cause a fall if the patient were standing will be analyzed separately. Accordingly, the analysis will focus on epileptic spasms, myoclonic seizures, and tonic seizures. Moreover, to ensure greater oversight of the reliability, caregivers will undergo a brief training on the correct classification and quantification of seizures. Specifically, the type of seizure experienced by the patient will be defined in collaboration with the physician, also using home videos and video-electroencephalographic recordings (videoEEGs) before starting the seizure diary.To identify indicator species—specific microbial taxa that are strongly associated with distinct microbial environments—which may serve as biomarkers to guide clinicians in selecting interventions with the highest likelihood of improving patient quality of life.

Secondary outcomes of the study are related to sleep disturbances and GI discomfort. Thus, we will consider:

Decreased Sleep SDSC scale (max score = 125) by at least 5%;Decrease GISI (max score = 17), by at least 2 points.

Both gastrointestinal and sleep disturbances are reported in over 80% of patients with CDKL5 deficiency disorder; therefore, we considered these changes to be clinically meaningful, even if modest in extent, also based on our clinical experience (15).

Other outcomes to be evaluated:

Global change from baseline, assessed by the Clinical Global Impression of Change (CGI-C), [ranging from 1 (very much improved) to 7 (very much worse), with a score of 4 indicating no change] decrease of at least 1 point;Caregiver burden by Parenting Stress Index (PSI-SF); clinically significance > 85%,Decrease by at least 5%.

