### Statistical analyses

We will examine longitudinal changes, with particular emphasis on differences between baseline (T0) and post-MF1 (T1), as well as between the second baseline following washout (T2) and post-MF2 (T3).

In descriptive analyses, data will be presented as mean ±SD for continuous variables and as percentages for categorical variables. The primary endpoint will be measured using the McNemar exact test. Differences in continuous variables (scale scores, biomarkers) will be tested using the unpaired and paired t-test for independent and dependent samples, respectively, in case of normally distributed data. For non-normally distributed data, the Wilcoxon rank-sum test will be used for independent samples, and the Wilcoxon signed-rank test for dependent samples. For comparisons among multiple time points, the ANOVA (or Kruskal-Wallis test for non-parametric data) will be applied to independent samples, while repeated measures ANOVA (or Friedman test for non-parametric data) will be used for dependent samples. When appropriate, a *post hoc* test (e.g., Bonferroni correction or Tukey’s HSD) will be performed to adjust the *p*-value.

A p-value < 0.05 will be considered statistically significant.

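### PSI-SF is scheduled only at T0 and T4, with no reading between MF1 and MF2, so its one change score mixes both products and is taken off product

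*Protocol article*

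**What the plan says.** The protocol article bears on this in five places.

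- **Study procedures, Table 1.** The row reads "Parenting Stress Index questionnaire (PSI-SF) (16) X x". The two marks stand under T0 and T4; T1, T2 and T3 are empty. The legend defines the columns: "T0, screening/baseline; T1, first supplementation (MF1); T2, wash-out period; T3, second supplementation (MF2); T4: wash-out period".
- **Efficacy endpoints, other outcomes.** The criterion is "Caregiver burden by Parenting Stress Index (PSI-SF); clinically significance > 85%,Decrease by at least 5" percent. No product and no period is named.
- **Trial design.** "This is a 32-week single-arm, open-label clinical trial", run as "a 12-week supplementation period with MF1, 4-week washout, 12-week supplementation with MF2, and a final 4-week washout". Besides baseline, complete clinical assessments are planned "after the first supplementation and at the end-of-treatment visit, 1 week after the last supplementation".
- **Statistical analyses.** The emphasis is on "differences between baseline (T0) and post-MF1 (T1), as well as between the second baseline following washout (T2) and post-MF2 (T3").
- **Abstract, Methods and analysis.** One primary objective is to "determine whether supplementation with ALAC/FOS/inulin alone or in combination with NaB can improve neurological features". Trial objectives puts the same alone-or-with-NaB question to seizure frequency.

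**The concern.** The trial gives two products one after the other, and its analysis section is built around one before/after contrast for each. PSI-SF has a response threshold but a single post-baseline reading, taken after both products have been given and stopped. A fall in parenting stress from T0 to T4 could reflect MF1, MF2, both, or simply time and contact with the study team. A benefit that was present during supplementation and then faded could be recorded as no response.

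At stake is whether this outcome can inform the MF1 and MF2 questions at all. The gap lies in data collection, so no later analysis can recover it. The primary and secondary outcomes and the sample size do not depend on it.

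**Working it through.** **1. Timeline.** The inputs are the four periods in Trial design. Their sum is 12 + 4 + 12 + 4 = 32 weeks, which reproduces the stated study length.

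| Period | Weeks |
|---|---|
| MF1 | 0 to 12 |
| First washout | 12 to 16 |
| MF2 | 16 to 28 |
| Final washout | 28 to 32 |

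**2. When the second PSI-SF reading falls.** The documents allow two readings.

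- *Table 1.* T4 is a washout period. Statistical analyses treats T2 as the baseline following the first washout. If T4 is likewise the end of its washout, it is week 32: 32 − 28 = 4 weeks after MF2 and 32 − 12 = 20 weeks after MF1.
- *Trial design.* The last complete assessment is one week after the last supplementation: 28 + 1 = week 29, so 1 week after MF2 and 29 − 12 = 17 weeks after MF1.

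On either reading the form is completed off product and after both products. The change spans about 29 to 32 weeks.

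**3. Contrasts that can be formed.** The inputs are the marks in Table 1 and the two contrasts in Statistical analyses.

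| Scale | Marks | T0 to T1 (MF1) | T2 to T3 (MF2) | T0 to T2 | T2 to T4 |
|---|---|---|---|---|---|
| PSI-SF | T0, T4 | no | no | no | no |
| GISI, SDSC, CGI-I, MBAS, CDD-SA | T0, T2, T4 | no | no | yes | yes |

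PSI-SF has a value at 1 of the 4 time points that the emphasised contrasts use (T0), and 0 of the 2 contrasts can be formed in any of the 20 patients. The five other clinical scales also give 0 of 2. With their T2 reading, however, each can be split into one interval holding MF1 and its washout and one holding MF2 and the off-product time before T4. PSI-SF allows no such split.

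**4. Mid-study assessment.** Trial design plans a complete clinical assessment after the first supplementation. Table 1 places the middle reading of the other clinical scales at T2 and gives PSI-SF none. Trial design does not name PSI-SF, so this is a poor fit rather than a flat contradiction.

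**The case against.** The strongest reply is that the protocol puts no product-specific question to caregiver burden. PSI-SF sits below the primary and secondary outcomes. Its 5% criterion names no product, while the two rounds of supplementation are named for the seizure outcome only. The abstract speaks of neurological features, which does not naturally cover parenting stress. Stressing two contrasts does not exclude others. A before/after reading of the whole programme is consistent with the text. This stands, and it is why the point is minor.

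Three stronger readings are tempting, and the documents do not support them.

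- *The form is certainly completed after the whole final washout, over 32 weeks.* The Table 1 legend says only that T4 is a washout period, and Trial design suggests about week 29. If the reading is one week off MF2, the worry about a fading benefit is much weaker.
- *PSI-SF alone is never read at the end of supplementation.* GISI, SDSC, CGI-I, MBAS and CDD-SA share that gap, and GISI and SDSC are the secondary outcomes. Among the outcome scales, only the missing T2 reading is particular to PSI-SF.
- *The 5% criterion cannot be evaluated.* It can, as an overall T0 to T4 change. What it cannot do is inform on either product.

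It is also fair that extra forms would not cure the lack of a control group, that families already keep a daily seizure diary and complete dietary surveys at all five time points, and that filling T1, T2 and T3 would measure PSI-SF more often than the secondary scales. These points bear on how many forms to add. They do not explain why PSI-SF should lack the mid-study reading that the other clinical scales have.

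**Conclusion.** The point holds, at low weight. As scheduled, PSI-SF yields one change score per family. That score mixes MF1 and MF2 in fixed order, without a control, and is read about 1 to 4 weeks after MF2. It supports 0 of the 2 emphasised contrasts and, unlike the other clinical scales, offers no division between the products.

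This rests on the Table 1 marks being complete as printed and on the stated period lengths. It does not depend on which timing of the last assessment is right, since both are off product and after both supplements; the two passages still have to be reconciled. It does not assume that the 5% criterion was meant per product. If only a whole-programme reading was intended, the schedule can deliver that, but then PSI-SF has no bearing on the MF1 and MF2 questions.

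**What to change.** - **Minimum:** add PSI-SF at the mid-study assessment between the products (T2), matching the other clinical scales. The T0 to T2 and T2 to T4 changes can then each be linked to one product and the off-product time after it.
- **Preferably:** also add it at the end of each supplementation (T1 and T3), so that T0 to T1 and T2 to T3 can be formed, and keep T4 as the washout reading. Consider T1 and T3 for GISI, SDSC, CGI-I, MBAS and CDD-SA at the same time, since they share that gap.
- **Reconcile** Trial design with Table 1 on when the mid-study and last clinical assessments take place, and state the week of T2 and T4.
- **Until readings are added,** report PSI-SF only as an overall before/after change, with no claim for either product. This wording alone does not close the gap.

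The cost is one to three extra caregiver questionnaires per family at existing time points: 20 × 1 = 20 to 20 × 3 = 60 forms over the trial if all 20 patients complete it. That is a small but real addition to the caregivers' load. The added changes would still be uncontrolled for time, study contact and expectation, so they would show which period a change belongs to without proving that the product caused it.

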### Subject withdrawal

Patient parents/legal guardians may decide to terminate the study at any time.

The principal investigator, guarantor of the study, may decide to terminate a patient’s participation at any time if the enrolled subject presents adverse events or is not compliant with the study procedures, or after withdrawal of participation consent.

### Data management

Case report forms (CRFs) will be completed for each enrolled study subject, with data consistently recorded on electronic CRFs in alignment with source documents. The data will be securely stored in a centralized data repository (Network Attached Storage) to ensure protection. Each subject will be assigned a unique ID for accurate tracking and management.

### Efficacy endpoints

The primary outcomes of the study are:

To evaluate the number of CDD patients considered treatment responders (seizure reduction ≥50%, ≥75% or ≥100% from baseline in monthly seizure counts) during the 12-week treatment period in 1st and 2nd round of supplementation. With regard to seizure counting, in order to improve its reliability, seizures characterized by a motor component of sufficient intensity and/or duration to potentially cause a fall if the patient were standing will be analyzed separately. Accordingly, the analysis will focus on epileptic spasms, myoclonic seizures, and tonic seizures. Moreover, to ensure greater oversight of the reliability, caregivers will undergo a brief training on the correct classification and quantification of seizures. Specifically, the type of seizure experienced by the patient will be defined in collaboration with the physician, also using home videos and video-electroencephalographic recordings (videoEEGs) before starting the seizure diary.To identify indicator species—specific microbial taxa that are strongly associated with distinct microbial environments—which may serve as biomarkers to guide clinicians in selecting interventions with the highest likelihood of improving patient quality of life.

Secondary outcomes of the study are related to sleep disturbances and GI discomfort. Thus, we will consider:

Decreased Sleep SDSC scale (max score = 125) by at least 5%;Decrease GISI (max score = 17), by at least 2 points.

Both gastrointestinal and sleep disturbances are reported in over 80% of patients with CDKL5 deficiency disorder; therefore, we considered these changes to be clinically meaningful, even if modest in extent, also based on our clinical experience (15).

Other outcomes to be evaluated:

Global change from baseline, assessed by the Clinical Global Impression of Change (CGI-C), [ranging from 1 (very much improved) to 7 (very much worse), with a score of 4 indicating no change] decrease of at least 1 point;Caregiver burden by Parenting Stress Index (PSI-SF); clinically significance > 85%,Decrease by at least 5%.

### Biomarker endpoints

The biomarkers evaluation will enhance our understanding of drug safety and its potential effects on both the microbiota and the brain. This investigation will assess the baseline composition of the microbiota and its changes following treatment by examining alpha and beta diversity, the relative abundances of bacterial and fungal taxa, and levels of SCFAs in fecal and DBS samples. Furthermore, clinical evaluations will provide a comprehensive view of patient health by considering disease severity, overall well-being and gastrointestinal improvements over time.

### Statistical analyses

We will examine longitudinal changes, with particular emphasis on differences between baseline (T0) and post-MF1 (T1), as well as between the second baseline following washout (T2) and post-MF2 (T3).

In descriptive analyses, data will be presented as mean ±SD for continuous variables and as percentages for categorical variables. The primary endpoint will be measured using the McNemar exact test. Differences in continuous variables (scale scores, biomarkers) will be tested using the unpaired and paired t-test for independent and dependent samples, respectively, in case of normally distributed data. For non-normally distributed data, the Wilcoxon rank-sum test will be used for independent samples, and the Wilcoxon signed-rank test for dependent samples. For comparisons among multiple time points, the ANOVA (or Kruskal-Wallis test for non-parametric data) will be applied to independent samples, while repeated measures ANOVA (or Friedman test for non-parametric data) will be used for dependent samples. When appropriate, a *post hoc* test (e.g., Bonferroni correction or Tukey’s HSD) will be performed to adjust the *p*-value.

A p-value < 0.05 will be considered statistically significant.

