### Participants

The study will enrol 20 CDD patients. The sample size for this study is dictated by the rarity of the condition, 1:40,000 live births (3), and considering that the number of CDD patients in Italy is about 60 (according to the report of the Patients Association “CDKL5 Insieme verso la cura”). The sample size is calculated based on the following assumptions: (1) the clinical success for an enrolled patient is defined as a reduction of at least 50% of the seizure frequency compared to baseline; (2) a clinically significant result is achieved if at least 35% of the enrolled patients reduce the seizure frequency by at least 50%.

With these premises, a McNemar exact test (“after vs. before”), applied to a sample of 20 subjects, reaches a power of 80%, less than an alpha-error of 5%, in verifying clinical success in 35% of cases, using the following inputs: percentage of positives that become negative = 0; percentage of negatives that become positive = 35.

Eligible patients from Italy who meet the defined inclusion and exclusion criteria will be recruited, after signing the informed consent.

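### Mean ± SD is set as the summary for all continuous variables, including those the plan expects to be non-normal and tests by ranks, so their reported size does not match what is tested

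*Protocol article*

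**What the plan says.** Three statements in the protocol article's Statistical analyses section bear on this point.

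- Summary, for descriptive analyses: "data will be presented as mean ±SD for continuous variables", with percentages for categorical ones.
- Scope and parametric tests: "Differences in continuous variables (scale scores, biomarkers) will be tested using the unpaired and paired t-test", for data that are normally distributed.
- Otherwise: "For non-normally distributed data, the Wilcoxon rank-sum test will be used for independent samples, and the Wilcoxon signed-rank test for dependent samples". For several time points, "repeated measures ANOVA (or Friedman test for non-parametric data) will be used for dependent samples".

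The section on biomarker endpoints shows which variables fall under this rule, among them "the relative abundances of bacterial and fungal taxa, and levels of SCFAs in fecal and DBS samples". The Participants section fixes the size: "The study will enrol 20 CDD patients". The article names no median, interquartile range, rank-based estimate or transformation.

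**The concern.** The plan allows for non-normality when it chooses a test but not when it chooses a summary. A variable sent to a signed-rank or Friedman test because it is skewed would still be tabulated as mean ± SD. The test would then concern the typical within-patient shift, while the number printed beside it would be pulled by the largest values.

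Taxon abundances and SCFA levels cannot fall below zero, so right skew is plausible for them. What is at stake is how the size of change in biomarkers and scores is reported. A small single-arm study that is meant to support further trials hands on such figures, and a reader planning the next study could take a size and a spread that reflect one or two patients.

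**Working it through.** The plan gives no figure on this point. Its one calculation, the McNemar power, concerns the responder endpoint and is not involved.

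**Inputs.** n = 20 (Participants). The rest is assumed, because the document gives no SDs or distributions: lognormal levels, between-patient log SD 0.7, 1.0 and 1.3, within-patient log SD 0.3 to 0.5 at each visit, and a true 1.3-fold rise.

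**Step 1: one visit.** For a lognormal variable with log SD σ, mean/median = exp(σ²/2) and SD/mean = √(exp(σ²) − 1). The SD equals the mean when σ² = ln 2 = 0.693, that is σ = 0.83, so the assumed range straddles that point. Between-patient spread alone gives the second column below. The third column is from simulated trials of 20 and includes the within-patient spread.

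| Between-patient log SD | exp(σ²/2) | Trials with SD > mean |
|---|---|---|
| 0.7 | exp(0.245) = 1.28 | about 14–28% |
| 1.0 | exp(0.5) = 1.65 | about 57–69% |
| 1.3 | exp(0.845) = 2.33 | about 86–90% |

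In the simulated samples the mean was about 1.3 to 2.2 times the median. Where the SD exceeds the mean, mean minus one SD is a negative level, which cannot occur.

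**Step 2: size of change.** Among simulated trials with a significant signed-rank test (p < 0.05), the mean raw change was typically 1.2 to 2.0 times the Hodges-Lehmann shift, the estimate that belongs to that test. The ratio rose with the skew.

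**Step 3: direction of change.** In the same significant trials the mean had the opposite sign to the Hodges-Lehmann shift in about 0 to 1%, and in no more than about 2% across repeat runs. With a wider assumed spread (median follow-up/baseline ratio 0.7, baseline log SD 0.5 to 1.5, log SD of the ratio 0.5 to 1.0) the share was 0.3% to 9.0%. For comparison, the first settings imply a log SD of the ratio of √2 × 0.3 = 0.42 to √2 × 0.5 = 0.71.

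**Step 4: can one patient do it?** Let 19 patients fall by amounts evenly spaced from 2 to 10 (average 6) and one rise by 150.

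- Mean change = (150 − 19 × 6)/20 = 36/20 = +1.8, with SD 35.0.
- Median = −5.8, and signed-rank p = 0.0007.
- Without that one patient the mean is −6.0.

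This case is constructed. It shows that reversal is possible, not how often it occurs.

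**Step 5: bounded scales.** On GISI (maximum 17), suppose 18 patients improve by 1, one is unchanged and one worsens by the full 17. The mean is (−18 + 17)/20 = −0.05, so the sign holds. It takes two patients worsening by 10 to give (−18 + 20)/20 = +0.1, with signed-rank p = 0.007. The problem is therefore mainly one for unbounded or strongly skewed biomarkers.

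**The case against.** The strongest reply is that the sentence governs descriptive analyses only. It does not make mean ± SD the estimate of change, and it does not rule out medians, paired differences or confidence intervals. Those details commonly sit in an analysis plan or full protocol that is not shown, so their absence from the article is no fault. This stands, and the point rests only on what the article does state: one summary for all continuous variables, beside tests that treat some of them as non-normal.

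The reply can add that no decision depends on this. The primary endpoint is a responder count under McNemar's test, and the secondary outcomes are threshold decreases on bounded scales. That also stands. So does the remark that an SD above the mean is a familiar warning of skew, and that all the skew here is assumed.

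A reader might infer more: that the published means would often contradict the test beside them. The documents and the arithmetic do not support that. With a true 1.3-fold rise, the sign of the mean change differs from that of the median within-patient ratio in about 2% to 18% of all simulated trials, but nearly all of these have non-significant tests, so there is no directional result to contradict. With no true change the disagreement is about 26% to 33%, which only reflects two estimates scattering around zero.

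**Conclusion.** The point holds as a mismatch between the stated summary and the stated tests. It is confined to the descriptive reporting of skewed biomarkers and scores. The harm to expect is a distorted size, not a reversed direction: under the assumed lognormal spread the SD exceeds the mean in about 14% to 90% of trials, and the mean change is typically 1.2 to 2 times the rank-based shift when the test is significant. Contradiction of a significant test is rare in those settings (about 0 to 1%) and reaches 9% only under the wider spread. If the biomarkers prove close to normal, little of this arises. Sample size, power, type I error and the responder analysis do not change. It is a minor point and a free improvement.

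**What to change.** In the Statistical analyses section, restrict mean ± SD to approximately normal variables. For any variable tested by a rank method, present median (IQR) by visit and the within-patient change as a Hodges-Lehmann estimate with 95% CI. For variables tested by paired t-test, add the mean within-patient difference with 95% CI.

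The contrasts are those the section already emphasises, T0 to T1 and T2 to T3. Table 1 does not mark every variable at all four visits: GISI and SDSC are marked at T0, T2 and T4, and dried blood spots at T0, T1 and T3. The contrast should therefore be named for each variable.

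The cost is a sentence or two and slightly longer tables. No test, visit, sample or data collection changes.

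### The primary McNemar test has one cell that is empty by definition, so it tests the responder rate against zero and not against the rate expected without an effective product

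*Protocol article*

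**What the plan says.** All references are to the Protocol article.

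- **Trial design:** "This is a 32-week single-arm, open-label clinical trial". There is no concurrent control.
- **Participants, definition of success:** "the clinical success for an enrolled patient is defined as a reduction of at least 50% of the seizure frequency compared to baseline". Efficacy endpoints likewise counts responders by their change from baseline in monthly seizure counts, in each of the two rounds.
- **Participants, clinical criterion:** "a clinically significant result is achieved if at least 35% of the enrolled patients reduce the seizure frequency by at least 50" per cent.
- **Participants, sample size:** an exact McNemar test of after versus before, "applied to a sample of 20 subjects", "reaches a power of 80%, less than an alpha-error of 5" per cent, with the inputs "percentage of positives that become negative = 0; percentage of negatives that become positive = 35".
- **Statistical analyses:** "The primary endpoint will be measured using the McNemar exact test", and "A p-value < 0.05 will be considered statistically significant". Whether the test is one-sided or two-sided is not stated.

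The article gives no background or reference responder rate.

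**The concern.** McNemar's test is for a yes/no state that is observed twice in each patient and can change in either direction. Its null is that the two directions of change are equally frequent. Here the state is itself a change from baseline, so it exists only after treatment. Every patient counts as negative before, and movement from positive to negative is impossible. Equal frequency of the two changes can then hold only if the true responder rate is zero.

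That is not the question of the trial. Seizure counts come from caregiver diaries in an uncontrolled, open-label study. Some patients may show a 50% fall through natural fluctuation, regression to the mean or expectation. The useful null is the proportion who would do so without an effective product. At stake is what a significant primary p-value means, and whether the nominal 5% error rate applies to the claim that readers will draw from it.

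**Working it through.** **Inputs.** From Participants: n = 20, positive to negative = 0%, negative to positive = 35%, alpha 5%, power 80%. From Statistical analyses: exact McNemar, p < 0.05. The background responder rate p0 is not given, so 10% to 25% is assumed as a range. All figures below are for a single test in one round.

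**1. The plan's own figure.** The two-sided normal-approximation formula for McNemar, with discordant total pd = 0.35 and difference d = 0.35, is

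N = (1.960 × √pd + 0.842 × √(pd − d²))² / d²

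= (1.960 × √0.35 + 0.842 × √0.2275)² / 0.1225 = 19.9, rounded up to 20.

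Power at n = 20 is 80.3%, so the stated 80% is reproduced, but by an approximation and not by the exact test that the plan names.

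**2. The exact test with one cell at zero.** With k responders and none in the opposite cell, the two-sided p-value is 2 × 0.5^k and the one-sided p-value is 0.5^k.

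| Responders k | Two-sided p | One-sided p |
|---|---|---|
| 4 | 0.125 | 0.0625 |
| 5 | 0.0625 | 0.031 |
| 6 | 0.031 | 0.016 |
| 7 | 0.016 | 0.008 |

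The test is significant from 6/20 (30%) if two-sided and from 5/20 (25%) if one-sided. The non-responders do not enter the p-value.

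**3. Power of the exact test as planned.** For X ~ Binomial(20, 0.35):

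- Two-sided: P(X ≥ 6) = 75.5%. The first n that reaches 80% is 22.
- One-sided: P(X ≥ 5) = 88.2%.

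**4. Error when the product does nothing.** If a share p0 would show a 50% fall anyway, the chance of reaching the threshold is P(X ≥ threshold) for X ~ Binomial(20, p0).

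| Assumed p0 | At least 6/20 (two-sided McNemar) | At least 7/20 (the 35% clinical criterion) |
|---|---|---|
| 10% | 1.1% | 0.2% |
| 15% | 6.7% | 2.2% |
| 20% | 19.6% | 8.7% |
| 25% | 38.3% | 21.4% |

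Solving P(X ≥ 6) = 0.05 gives p0 of about 14.0%; solving P(X ≥ 6) = 0.025 gives about 11.9%.

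**5. Power with an explicit reference rate.** Exact binomial test, n = 20, one-sided 0.025, true rate 35%:

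| Reference p0 | Responders needed | Power |
|---|---|---|
| 10% | 6/20 | 75.5% |
| 15% | 7/20 | 58.3% |
| 20% | 9/20 | 23.8% |

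**The case against.** **A legitimate McNemar table is available.** Responder status in round 1 against round 2 would be a proper paired comparison. The article does not describe that test. The sample-size paragraph specifies after versus before and sets one direction to zero, and Statistical analyses stresses each round against its own starting point.

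**The background rate may be low.** The Introduction describes the epilepsy as highly refractory, and entry requires four weeks on a stable drug regimen. Below about 12% the 6/20 rule has an error of no more than 2.5%. This stands as a limit on the size of the problem. It does not repair the test, because the article neither states nor justifies such a rate, and it gives no support for 20% or 25% either.

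**The weakness belongs to the design.** Fluctuation, regression to the mean and caregiver expectation affect any uncontrolled open-label study, and a binomial test against a chosen rate does not remove them. That is correct. The gain is that the comparison becomes explicit and open to challenge, where the present test hides it.

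**A reader might infer that the plan contradicts itself,** because 6/20 is statistically significant while the clinical criterion needs 7/20. The text does not support this. It sets a statistical and a clinical threshold for different purposes, and by its own wording 6/20 would not be a clinically significant result. Under the 7/20 criterion the errors are those in the right-hand column of the error table.

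**Conclusion.** The point holds. The primary test is wrongly specified: one cell is empty by definition, the p-value is a function of the responder count alone, and the null is a responder rate of zero. No other part of the article supplies a relevant comparison.

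The consequence is conditional. With a two-sided test, the chance that an ineffective product is significant exceeds 5% once the background rate is above about 14%. That rate is unknown, and every p0 used here is an assumption. If the test is one-sided the bar is lower, at 5/20.

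A reader might go further and conclude that a significant result would be no evidence of efficacy at all. The documents do not support that: if the background rate were 10%, the 6/20 rule would err only 1.1% of the time. What can be said is that the p-value does not itself test efficacy against background change.

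Separately, the stated 80% power is that of the normal approximation. The named exact test, two-sided, has 75.5% at a true rate of 35%.

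**What to change.** In Participants and Statistical analyses, replace the McNemar test with the following.

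- The responder proportion at the 50% threshold among the enrolled patients, reported separately for each round with an exact (Clopper-Pearson) 95% confidence interval. For scale, 6/20 gives 11.9% to 54.3% and 7/20 gives 15.4% to 59.2%.
- An exact binomial test of that proportion against a reference rate that is justified on clinical grounds and fixed before any data are seen, with sidedness stated. The rate should not be set at 15% merely because the interval for 7/20 happens to exclude it.
- A sentence saying that this comparison does not replace a control group.

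Restate the power for the chosen reference rate. **The cost is a less favourable figure:** at a true rate of 35% and one-sided 0.025, power is 75.5% for a reference of 10%, 58% for 15% and 24% for 20%, so the 80% claim cannot be kept at n = 20 for any of these. The change is otherwise to wording and analysis only, with no extra patients or procedures.
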